#### Primary Outcome Measures

Change in depressive symptoms from baseline (T0) to 12 weeks (T1) and 26 weeks (T2) was assessed using the clinician-administered HDRS-17, which was validated in Spanish [23,24]. The HDRS-17 total score ranges from 0 to 52, with higher scores indicating more severe depression.

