#### Secondary Outcome Measures

Secondary outcomes will include changes from baseline (T0) to 12 weeks (T1) and 26 weeks (T2) in overall functioning, health-related quality of life, perceived stress, and menstruation-related distress.

Overall functioning: Assessed via the self-administered World Health Organization Disability Assessment Schedule 2.0 (WHODAS 2.0; 36-item version) [25,26]. It evaluates functioning across 6 domains, with higher scores indicating greater disability.Health-related quality of life: Measured by the self-reported EuroQol 5-Dimension 5-Level (EQ-5D-5L) [27,28], which assesses 5 dimensions of health on a 5-point scale. Responses are combined into a single index value ranging from below 0 (health states worse than death) to 1 (full health). A visual analogue scale is also included, ranging from 0 (worst imaginable health) to 100 (best imaginable health).Perceived stress: Evaluated using the self-reported Perceived Stress Scale (PSS) [29,30]. Items are rated on a 5-point Likert scale from 0 (never) to 4 (very often), yielding a total score from 0 to 56. Higher scores reflect greater perceived stress.Menstruation-related distress: Assessed via the 25-item self-reported Menstrual Distress Questionnaire (MEDI-Q) [31]. It evaluates symptoms such as pain, discomfort, psychological changes, gastrointestinal symptoms, and physiological alterations.

All instruments, except for the MEDI-Q, will be used in their Spanish validated versions. As the MEDI-Q is a recently developed tool not yet validated in Spanish, its use in this study provides an opportunity for initial cultural adaptation within this population.

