### Data Analysis

#### Sample Size Calculation

A total sample size of 120 participants (60 per group) is required. This estimation was calculated based on a design with 2 groups and 3 measurement points. Assuming an effect size of *f* of 0.15, a significance level of *α* of .05, and a power of 0.90, with a correlation among repeated measures of 0.5 and assumed sphericity (*ε*=1), the minimum sample size estimated was at 96 patients. This number was increased to 120 to account for an anticipated 20% attrition rate. The sample size was determined using G*Power version 3.1.7.

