#### Outcome Analysis and Longitudinal Modeling

Primary and secondary outcomes will be analyzed using an intention-to-treat (ITT) approach, with all participants analyzed according to their original randomization group. Linear mixed-effects models (LMMs) will be used to examine changes over time and between groups for the HDRS-17, WHODAS 2.0, EQ-5D-5L, PSS, and MEDI-Q scores. These models will include fixed effects for group, time, and their interaction, with a random intercept for participants to account for within-subject correlation over time.

While change scores may be calculated for descriptive or interpretative purposes, the LMMs will serve as the primary inferential approach. In the event of a significant group × time interaction, post hoc simple effect analyses will be conducted to evaluate between-group differences at a specific time point and within-group changes from baseline, using estimated marginal means with appropriate corrections for multiple comparisons.

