#### Predictors and Covariate Analysis

Additional analyses will identify baseline predictors of clinical improvement using LMMs and multiple linear regression. To address the dynamic nature of psychological factors, perceived stress (PSS) and menstrual distress (MEDI-Q) will be modeled as time-varying covariates within the LMM framework rather than as static baseline moderators. This allows for the assessment of whether longitudinal fluctuations in these variables are associated with concurrent changes in depressive symptoms. Furthermore, exploratory multilevel mediation analyses may be conducted to examine if changes in PSS or MEDI-Q partially mediate the intervention’s effect on HDRS-17 trajectories.

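### If the MEDI-Q is scored undivided, its psychological content can by itself produce part of any association or mediation with HDRS-17; a companion run without those items is needed before calling it a menstrual-symptom link

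*Protocol article*

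**What the plan says.** Under Predictors and Covariate Analysis, the protocol article states that "perceived stress (PSS) and menstrual distress (MEDI-Q) will be modeled as time-varying covariates within the LMM framework rather than as static baseline moderators". The purpose given is to see "whether longitudinal fluctuations in these variables are associated with concurrent changes in depressive symptoms". The same paragraph adds that "exploratory multilevel mediation analyses may be conducted to examine if changes in PSS or MEDI-Q partially mediate" the effect of the intervention on HDRS-17.

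Secondary Outcome Measures describes the MEDI-Q as a 25-item self-report questionnaire: "It evaluates symptoms such as pain, discomfort, psychological changes, gastrointestinal symptoms, and physiological alterations". The outcome in these models is the primary measure; Primary Outcome Measures says that change in depressive symptoms "was assessed using the clinician-administered HDRS-17".

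On scoring, Outcome Analysis and Longitudinal Modeling lists "HDRS-17, WHODAS 2.0, EQ-5D-5L, PSS, and MEDI-Q scores" as the quantities to be modelled. It names neither a MEDI-Q total nor a subscale. Nothing in the article separates psychological from bodily MEDI-Q items or mentions their overlap in content with HDRS-17.

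**The concern.** Psychological symptoms contribute to the covariate, and depressive symptoms are the outcome. A woman whose mood improves may score lower on both instruments whatever happens to her pain or gastrointestinal symptoms. A positive MEDI-Q coefficient then has two explanations that the planned model cannot separate: menstrual symptoms move with depression, or mood items move with a mood scale.

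The optional mediation analysis is more exposed. If the program improves mood, it can lower the psychological MEDI-Q items (treatment to mediator), and those items track HDRS-17 (mediator to outcome). An indirect effect through menstrual distress could then appear with no change in bodily symptoms. The trial's rationale is sex- and gender-specific contributors to depression, so readers would notice such a result.

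**Working it through.** **The plan's own figure.** The point disputes no stated number, but the check uses the planned 96 women, so that figure was reproduced first. The design is described as "based on a design with 2 groups and 3 measurement points", with f = 0.15, α = .05, power 0.90, correlation 0.5 and ε = 1. For the within-between interaction:

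- λ = N·f²·m/(1−ρ) = 96 × 0.0225 × 3 / 0.5 = 12.96
- degrees of freedom (2−1)(3−1) = 2 and (96−2)(3−1) = 188
- power = 0.902, and 96 is the smallest even N that reaches 0.90
- attrition: 96/(1−0.20) = 120

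Both stated figures are confirmed.

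**Assumptions, none given in the documents.** Write the MEDI-Q score as a psychological part plus a bodily part. Let w be the psychological share of its variance and r the correlation of the psychological part with HDRS-17. The bodily part is taken as unrelated to HDRS-17, to see what shared content can do alone. The correlation of the undivided score with HDRS-17 is then r·√w.

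**Simple version: one change score, 96 women, Fisher z.** The chance of P<.05 is about Φ(atanh(r√w)·√93 − 1.96).

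| r | w | r√w | chance of P<.05 |
|---|---|---|---|
| 0.4 | 0.1 | 0.13 | 23% |
| 0.4 | 0.2 | 0.18 | 41% |
| 0.4 | 0.3 | 0.22 | 57% |
| 0.6 | 0.1 | 0.19 | 46% |
| 0.6 | 0.2 | 0.27 | 76% |
| 0.6 | 0.3 | 0.33 | 91% |

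**Version closer to the planned model.** HDRS-17 was simulated on group, visit, their interaction and the covariate, with a random intercept, for 96 women at three visits, 200 runs per setting. Between- and within-woman variances were equal, which gives the 0.5 correlation of the sample size section. Here r is the within-woman correlation. Share of runs with P<.05 for the undivided score:

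| w | r = 0 | r = 0.3 | r = 0.5 | r = 0.7 |
|---|---|---|---|---|
| 0.1 | 5.5% | 27% | 52% | 81.5% |
| 0.2 | 8% | 36.5% | 82.5% | 99.5% |
| 0.4 | 9% | 74.5% | 98% | 100% |

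For r of 0.3 to 0.7, r√w runs from about 0.09 to 0.44.

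With the bodily part alone as covariate, P<.05 occurred in 2.5% to 8.5% of runs. The 12 settings average 70.5%/12 = 5.9%. At a true 5%, one setting of 200 runs has a standard error of √(0.05 × 0.95/200) = 1.5 percentage points, so these rates are close to nominal, with a few settings slightly high. The excess for the undivided score at r > 0 comes from the psychological part.

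**Mediation.** No figure was computed. The logic is the product of two paths: if treatment shifts only the psychological part, the treatment-to-mediator path is that shift, the mediator-to-outcome path is non-zero through r, and the product is non-zero although the bodily part never moved.

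**The case against.** The strongest reply is that the article makes no claim about bodily symptoms. It introduces PSS and MEDI-Q together as psychological factors and asks only whether they move with HDRS-17. On that reading, psychological content belongs to the construct and is not contamination. This stands as far as the stated question goes: the model answers whether the two measures move together. It does not license the further step of calling the link menstrual as distinct from mood.

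A reader might infer that the total score is certain to be used. The article says only scores, and an analysis plan that is not shown may name subscales. A reader might also infer that the model is bound to find an association. The check does not support that: at its low end the chance is 23% in the simple version and 27% in the simulation, and every input beyond the sample size is assumed. The degree of overlap is likewise undocumented, since the article lists no items for either scale, and one is self-reported while the other is clinician-administered.

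Finally, replacing the full score by a partial one would narrow the construct and would stop the mediation analysis from testing psychological menstrual distress as a pathway. That objection stands, and it is why the partial score should accompany the full one and not replace it.

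**Conclusion.** The point holds as a limit on interpretation. If the undivided MEDI-Q score is used, some of any association or indirect effect with HDRS-17 can arise from shared mood content, with no link to bodily menstrual symptoms. The size is unknown: the 27% to 100% range illustrates what the assumed shares and correlations would do and is not an estimate for this trial. It also rests on the assumption that bodily items are unrelated to HDRS-17.

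The reach is small. These analyses are labelled additional, and the mediation is exploratory and optional. A reader might infer that the efficacy result is compromised; it is not. The group-by-time test on HDRS-17, the analysis of the MEDI-Q as a secondary outcome and the sample size do not depend on this choice. This is an inexpensive improvement and not a defect that threatens the trial.

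**What to change.** Keep the full MEDI-Q score in the covariate and mediation models as planned, and keep it as the secondary outcome. In the analysis plan:

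- Prespecify a companion run of the covariate model, and of any mediation model, with a MEDI-Q score that leaves out the psychological items.
- Fix the allocation of items to psychological or other before analysis.
- Report both versions side by side.
- Attribute a link or mediation to menstrual symptoms as distinct from mood only if it also holds without the psychological items.

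The cost is a short addition to the plan, an item-allocation rule and a re-scoring of responses that the trial collects anyway. The article reports 8 women enrolled as of April 2026 and no analysis begun, so prespecification is still credible. The downside is that the partial score is non-standard and covers a narrower construct. It therefore serves as a sensitivity analysis. The loss of standard scoring weighs less here because the article itself says: "As the MEDI-Q is a recently developed tool not yet validated in Spanish".

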#### Metabolomics

Partial least squares regression and multiple regression analyses will be used to model associations between metabolite profiles, their changes over time, and changes in depressive symptoms. Variable importance in projection scores and cross-validation techniques will be used to evaluate model performance and identify key predictive biomarkers. Additionally, metabolomic changes will be assessed through exploratory factor analysis, grouping variables into latent factors. It should be noted that the study was originally conceptualized and powered as a confirmatory superiority RCT; therefore, the metabolomics substudy should be considered secondary and may be limited by this design. Nevertheless, given the scarcity of data in this biological field of research, we believe it is worthwhile to conduct this post hoc exploratory proof-of-concept study.

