### Biological Samples

#### Sample Types and Collection Procedures

Biological analysis will be conducted exclusively on specimens collected from cisgender women participants. Biological specimens to be collected include plasma, urine, saliva, fingernails, and hair. All collection procedures will adhere to standard operating procedures, with participant safety and comfort as priorities. Specific procedures for each biological sample are as follows:

Plasma: Blood samples will be collected using EDTA K2 plastic tubes (13 × 75 mm, 4 mL). Two tubes (totaling 8 mL) will be collected per participant on the day of the assessment visit.Urine: Participants will self-collect approximately 50 mL of midstream urine the night before their scheduled assessment visit, using a sterile 60-mL polypropylene container. The sample will be refrigerated overnight at the participant’s home and transported to the research facility on the day of the visit.Saliva: Participants will self-collect saliva samples the night before the assessment visit using 2 Salivette Cortisol collection devices. Samples will be refrigerated overnight at the participant’s home and transported to the research facility on the day of the visit.Fingernails: Participants will clip the distal ends of their fingernails at home before the assessment visit. Samples will be collected in sealed paper envelopes.Hair: A strand of hair (approximately 0.5 cm in diameter, or 50 mg for short hair) will be cut from the posterior vertex as close to the scalp as possible by trained personnel. The root end will be marked with a hair tie. Samples will be collected in sealed paper envelopes.

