#### Analytical Methods

The quantification of targeted metabolites in the tryptophan and steroid hormone pathways will be conducted using liquid chromatography-tandem mass spectrometry (LC-MS/MS) across all available biological matrices. This includes the measurement of tryptophan, kynurenine, serotonin, kynurenic acid, and relevant metabolic ratios (eg, kynurenine or tryptophan), as well as estradiol, testosterone, progesterone, cortisol, and their derivatives (eg, 20α-DHE, 20β-DHE). Data acquisition and processing will be performed using MassLynx 4.2 (version 4.2; Waters Corp.) and the TargetLynx application manager (Waters Corp.). To minimize interbatch variability, all samples will be analyzed in a single run once collection is complete. Given the sample size, biomarker analyses will be considered exploratory and hypothesis-generating, and the study is not powered to detect definitive associations.

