## Discussion

This RCT will evaluate the efficacy of the 3D Program, a gender-sensitive, guided iCBT intervention for women with moderate depressive symptoms. In addition to assessing clinical symptom reduction, the study also aims to investigate the potential biological mechanisms of treatment response through metabolomic and hormonal analyses. To our knowledge, this is among the first online psychological interventions specifically designed for women with depressive symptoms outside the perinatal period. Given that depressive symptoms disproportionately affect women and are shaped by both biological and sociocultural factors, the 3D Program addresses a longstanding gap in accessible, inclusive, and gender-sensitive mental health care. The intervention content was cocreated with women with lived experience of depressive symptoms—an approach that enhances ecological validity and acceptability of the program. This participatory approach may also improve uptake and real-world sustainability if efficacy is demonstrated.

A novel feature of this trial is the seminal search for the role of sex hormones and glucocorticoids in moderating treatment effects. The integration of metabolic profiling, focusing on tryptophan and steroid pathways, may offer preliminary insights into biological factors associated with individual differences in treatment response. This exploratory approach aligns with emerging models of personalized psychiatry and may contribute to the identification of biomarkers associated with therapeutic efficacy in depression treatment.

If effective, the 3D Program could serve as a cost-efficient and scalable adjunct to routine care within the public Spanish National Health System, with potential for adaptation and implementation in other publicly funded health care systems. It could reduce clinician burden and broaden access to evidence-based care, while empowering users through enhanced self-management. Its practical implementation—with therapist training deliverable in a single workshop—supports feasibility for integration into standard care pathways. Moreover, the modular and adaptable design of the program may facilitate future use in other populations, including older women and gender-diverse individuals. It may also allow integration with complementary care modalities such as pharmacotherapy or face-to-face psychological interventions, thereby broadening its applicability and impact.

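### The Discussion speaks of hormones moderating treatment effects, but the metabolite and predictor analyses as described name no marker-by-arm term and cannot separate prognosis from moderation; cycle phase at sampling is a separate gap.

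*Protocol article*

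**What the plan says.** **Aim.** The Discussion calls a novel feature of the trial its search for "the role of sex hormones and glucocorticoids in moderating treatment effects". The Abstract and Study Design are more modest and refer to predictors of, or metabolic signatures associated with, treatment response.

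**Models.**
- Metabolomics: partial least squares and "multiple regression analyses will be used to model associations between metabolite profiles, their changes over time, and changes in depressive symptoms". Arm is not mentioned.
- Predictors and Covariate Analysis: "Additional analyses will identify baseline predictors of clinical improvement using LMMs and multiple linear regression". No predictor-by-arm term is named. Perceived stress and menstrual distress "will be modeled as time-varying covariates within the LMM framework rather than as static baseline moderators".
- Outcome Analysis and Longitudinal Modeling: "These models will include fixed effects for group, time, and their interaction, with a random intercept for participants". Group by time is the only interaction stated in the article.

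**Sampling.** Analytical Methods lists tryptophan metabolites "as well as estradiol, testosterone, progesterone, cortisol, and their derivatives". Blood is drawn at the visit ("Two tubes (totaling 8 mL) will be collected per participant on the day of the assessment visit"); urine and saliva are self-collected the night before. Table 1 places samples at T0, T1 and T2 but the gynecological visit, where menstrual history is taken, at T0 only. Cycle phase and hormonal contraception are named nowhere.

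**Status.** Analytical Methods and Metabolomics both describe the biomarker work as exploratory, and the former says that it is not powered for definitive associations.

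**The concern.** Improvement in a pooled sample is not response to the 3D Program. Both arms receive treatment as usual and the control arm also receives videos, so women may improve without the program. A metabolite that tracks improvement equally in both arms is prognostic. A moderator is a baseline marker whose relation to outcome differs by arm, and only a marker-by-arm term estimates that difference. Metabolite changes after baseline are measured after randomization, may themselves be affected by treatment, and cannot serve as moderators. The randomized control arm makes the right contrast available, but the described models do not use it.

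Cycle phase is a separate matter. Estradiol and progesterone vary over the menstrual cycle, and the participants are aged 18 to 45. The Eligibility section excludes pregnancy, and age above 45, on grounds of hormonal confounding. The same reasoning applies to cycle phase and hormonal contraception. If these go unrecorded, steroid levels and their changes carry noise from the timing of visits, and possibly confounding if mood also varies with phase.

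**Working it through.** **1. The plan's own figure.** Inputs from Sample Size Calculation: f=0.15, two groups, m=3 measurements, correlation 0.5, sphericity, alpha 0.05, power 0.90. For the group by time test, lambda = f²·N·m/(1−rho) = 0.0225×96×3/0.5 = 12.96, with 2 and (96−2)×2 = 188 degrees of freedom. Power is 0.902; at N=94 it is 0.896. So 96 is the minimum, and 96/0.8 = 120. Both figures reproduce. They concern group by time only and say nothing about moderation.

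**2. What a pooled model can distinguish.** The simulation used 4,000 runs per case, 96 completers in equal arms, a standard-normal marker, residual SD 1, an arm effect of 0.5 and a two-sided 0.05 level. The arm effect and slopes are assumptions, not document figures. The pooled model regresses the outcome on the marker alone; the interaction model contains marker, arm and marker×arm.

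| Truth (slope in control, 3D arm) | Pooled model significant | Interaction significant |
|---|---|---|
| Purely prognostic (0.3, 0.3) | 79% | 5% |
| Moderator (0, 0.6) | 76% | 81% |
| Opposite slopes (−0.3, 0.3) | 5% | 81% |
| Null (0, 0) | 5% | 5% |

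The pooled model gives nearly the same answer in the first two rows and does no better than chance in the third.

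**3. What the interaction could detect.** For a one-degree-of-freedom interaction in a four-parameter regression with equal arms, the slope difference is 2√f², and partial R² is f²/(1+f²).
- 96 analysed, 80% power: f²=0.0835; partial R² = 0.0835/1.0835 = 7.7%; slope difference 2√0.0835 = 0.58 residual SD per marker SD.
- 96 analysed, 90% power: partial R² 10.1%, slope difference 0.67.
- 120 analysed, 80% power: partial R² 6.2%, slope difference 0.52.

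These are for one marker, before any multiplicity correction. The usable number may be below 96, because biological analysis is restricted to cisgender women and participants may decline individual sample types.

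**4. Cycle phase as noise.** Start from the moderator case above and multiply the slope by the square root of an assumed marker reliability. At reliability 1, 0.7, 0.5 and 0.3, interaction power is about 81%, 66%, 53% and 34%. The test is weakened but still possible.

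**5. Cycle position of the visits.** T1 and T2 are 14 weeks (98 days) apart on either clock in the article. For assumed cycle lengths of 25, 28, 30 and 35 days that is 98/25=3.92, 98/28=3.50, 98/30=3.27 and 98/35=2.80 cycles. From T0 to T1 the text gives 84 days, while Table 1's week numbers (2 to 12) give 70. A 28-day cycle gives 3.0 or 2.5 cycles and a 35-day cycle 2.4 or 2.0. The offset between visits therefore varies from woman to woman and cannot be reconstructed from the calendar.

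**The case against.** The strongest reply is that the article is condensed. It does not list the terms of the predictor models, and an interaction or covariate list could stand in an analysis plan that is not shown. That stands in part: the text is silent and does not rule an interaction out. But it describes these analyses in some detail (variable importance scores, cross-validation, factor analysis, mediation), and what it describes is association, while the Discussion speaks of moderation. That mismatch lies within the text itself.

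It is also fair that moderation appears in one Discussion sentence, that the sentence after it retreats to preliminary insights into associated factors, and that the work is labelled exploratory and unpowered. This lowers the stakes. The label excuses imprecision, but not a model that estimates a different quantity.

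On hormones, Participant Characteristics and Clinical Data provides for menstrual and reproductive history and says data will be used to adjust for confounding. That gives a basis at T0, but not at T1 or T2.

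Three stronger readings are tempting and not supported:
- That a pooled association will be reported as moderation. No section says so.
- That missing cycle phase itself makes moderation untestable. It adds noise and possible confounding; the absent marker-by-arm term alone carries that conclusion.
- That a particular visit falls in the opposite phase from baseline. This holds only for an assumed 28-day cycle and reverses at other plausible lengths.

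**Conclusion.** The point holds as a mismatch between one stated purpose and the analyses described. Followed as written, the metabolite and predictor models cannot separate prognostic markers from moderators of response to the 3D Program. The size of the problem depends on assumed slopes: with a common slope of 0.3 and 96 completers, a marker with no moderating role is significant in 79% of pooled analyses, against 5% for the interaction. Those figures describe a single-marker regression and illustrate the issue; they are not error rates of the planned partial least squares analysis.

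The gap on cycle phase and contraception is real but secondary. How much of the variation in sex steroids it explains cannot be derived from the documents. It is the more urgent of the two only because model wording can still be changed later, whereas cycle information not collected at the visit may not be recoverable. Eight women had been enrolled by April 2026.

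Neither matter touches the primary analysis or the sample size of 120.

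**What to change.** 1. For a short, pre-named list of baseline metabolites, add an exploratory HDRS-17 model with group, time, metabolite and the metabolite×group (×time) interaction. Where T0 is one of the modelled outcomes, the three-way term is the one that addresses moderation of change. Base any statement about moderation or treatment response on that interaction alone, reported with its confidence interval.
2. Call pooled associations, including all those with metabolite changes after randomization, prognostic or associative. If no interaction model is wanted, limit the Discussion wording to association with outcome.
3. Ask the date of last menses and current hormonal-contraceptive use at each sampling visit (T0, T1, T2), and adjust the sex-steroid models for cycle phase and contraceptive status.

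The cost is analysis-plan wording and two questions at visits already scheduled. The interaction estimates will be imprecise, and the more so after any multiplicity correction; that should be stated, and it is consistent with the exploratory status the article already gives this work.
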